### Statistical methods

Statistical analyses will be performed by using SPSS (SPSS Inc., Chicago, IL, USA). Baseline data of the two groups will be compared by Fisher’s exact and Wilcoxon rank-sum tests as well as two samples *t* test. Primary and secondary key analysis will be carried out according to the intention-to-treat principle, and hazard ratio and 95 % confidence interval values determined. The likelihood ratio will be calculated by using Cox proportional hazards regression analysis as bilateral *P* value. Peri-operative data, including measurements and procedure types, will be analyzed at recruitment completion. Survival data will be analyzed only at trial end.

### Termination criteria

The patient has the right to terminate the research and evaluation at any time point. Exit criteria include voluntarily exit without sacrificing further medical treatment; safety issues; severe violation of the designed program by the patient; recruitment problems, such as patient not meeting the inclusion criteria; and loss to follow-up.

### Termination program

The reasons and any possible adverse events shall be inquired from patients who decide to terminate the study, and the observation and evaluation shall be performed by the researcher *per se* if possible. Serious or unexpected adverse events shall be closely followed up. The researcher should try as much as possible to acquire patient information from the concerned individual to complete the final evaluation, and the efforts should be recorded as well. The evaluation and observation report as well as the causes of exit described by patients should be recorded as primary data. The major causes of exit will be kept in CRF, and the subsequent procedures, such as follow-up examination after discharge, should be completed as much as possible.

## Discussion

The development course of the surgical procedure for NSCLC has been quite similar to that of breast cancer, going through a revolution from extensive resection to better organ preservation. The history of lung cancer operation began with pneumonectomy, which was first performed by Gramham in 1933 [35] and then regarded as a standard procedure. Later, in the 1960s, it was demonstrated that lobectomy could yield equivalent radical therapeutic effects while achieving better preservation in lung function compared with pneumonectomy. Thereafter, anatomical lobectomy in combination with lymph node dissection or sampling has become the standard surgical approach for NSCLC [36].

Thanks to the application of CT scan, an increasing number of asymptomatic NSCLC cases, even those with an ‘inert’ biological behavior, are identified at an early stage. Therefore, sublobar resection, including wedged resection and segmentectomy, has attracted academic attention. A comparative study on lobectomy and sublobar for stage I NSCLC, conducted by the LCSG, is the only randomized controlled trial so far and was completed and published in 1995. Their findings suggested that local recurrence is increased threefold in sublobar resection compared with lobectomy, and long-term survival rate was also slightly lower in sublobar resection, although there was no statistically significant difference [10]. The study confirmed the therapeutic effect of lobectomy and refuted sublobar resection; however, this conclusion remains highly controversial because the enrolled tumor size was considered too large for the sublobar resection group [37].

On the other hand, as the LCSG study implied that sublobar resection might not be suitable for all NSCLC patients with tumor size of less than 3 cm, sublobar resection might be more suitable for NSCLC with smaller size or for patients with high-risk factors as a ‘compromised’ option. That is how the two mainstream viewpoints for sublobar resection emerged and influenced the subsequent studies. Accumulating retrospective studies have compared sublobar resection and lobectomy in terms of long-term therapeutic effects [10, 24–26, 38–61]. Their results suggested that sublobar resection could achieve similar long-term outcomes as standard lobectomy for patients with early-stage NSCLC (diameter of not more than 2 cm) [40, 44, 45, 50–53, 55, 59, 61]; on the other hand, lobectomy may not convey more beneficial effects for the elderly with NSCLC of not more than 3 cm [24, 25, 39, 43, 47, 48, 57, 62]. However, prospective randomized controlled trials to support these assumptions are scarce.

Two randomized controlled trials assessing sublobar resection for less advanced NSCLC have been launched: CALGB140503 [63] (US) and JCOG0802 [37] (Japan). Both of them aim to verify the radical therapeutic effects of sublobar resection for NSCLC with a diameter of not more than 2 cm. Given that ‘radical effect’ is the focus of both trials, they may not elicit high-quality supportive evidence on the priority of sublobar resection for elderly patients, in whom sublobar resection may match radicalness with compromise.

Radical surgery may not convey sufficient benefits given the limited life expectancy of elderly patients. In addition to concurrent diseases and declined organ function, radical surgery is very likely to increase the operation risk. Therefore, a reasonably balanced strategy considering radical effect, operation risk, and life quality is needed for elderly patients with NSCLC. However, elderly patients with lung cancer are under-represented by far, and the present study is the first prospective randomized controlled trial on elderly patients with NSCLC at an early stage.

Given the complexity of life expectancy and operation risks, CGA is adopted in the present study to differentiate from trials evaluating young patients, in order to facilitate stratified randomization and analysis.

There are two parts of CGAs, the 4-year survival scale of Lee et al. [64] and CGA, which evaluate the benefit of operation by life expectancy and the intervention by operation risk, respectively.

First of all, non-tumor-caused death is common in elderly patients with early NSCLC, which indicates the need for stratification. However, such relevant studies to serve as references to the present study are rare. The 4-year mortality in the American cohort was analyzed by Lee et al., who also established the 4-year survival scale [64], which is consistent with a review published in *JAMA* (2012) [30]. Therefore, the 4-year survival scale established by Lee et al. was adopted in the present study as the standard of stratification. Patients will be classified into four groups: low risk (score of between 0 to 5 and 4-year mortality of 4 %), moderate risk (score of between 6 and 9 and 4-year mortality of 15 %), high risk (score of between 10 and 13 and 4-year mortality of 42 %), and extremely high risk (score of more than 14 and 4-year mortality of 64 %).

In the present study, the elderly patients fulfilling the operation criteria will undergo CGA, which is a multidisciplinary comprehensive assessment for the elderly, including assessments of organ function, concurrent diseases, cognitive function, psychological state, social and economic issues, syndromes, medications, and nutritional status. Recent studies showed that CGA could predict death and complication risks [65]. Although the CGA procedure is complex, its feasibility has been proven by the CALGB 360401 clinical trial [66].

Based on CGA, the PACE scale proposed by Audisio et al. in 2003 was particularly designed for elderly patients with tumor undergoing operation [67]. The PACE scale is a reinforced CGA and includes CGA, brief fatigue inventory, performance status, instrumental activities of daily living, activities of daily living, and the ASA scale. The PACE scale has a predictive value in elderly patients undergoing surgical operation, as demonstrated by multiple-center clinical validation [68].

Given the complexity of the CGA procedure, our lack of experience in geriatric assessments, and lack of practice on standardized and large-scale trials, the participants of the present study will be screened first by the VES-13 scale before CGA. VES-13 is a self-checklist, including age and 12 items of self-assessment concerning health and organ function. Compared with conventional CGA, VES-13 is more convenient and is capable of predicting the vulnerability of elderly patients and can be used as a pre-screening tool for CGA [31, 32]. In the present study, patients with a score of at least 3 will be considered high-risk subjects and followed up with PACE evaluation.

The present study is so far the only prospective, multicenter, randomized controlled trial comparing sublobar resection and lobectomy for elderly patients that aims to identify the most appropriate surgical approach for NSCLC at an early stage, to find the balance between radical effect and operation risk, and to assess survival period and life quality.

If the proposed study hypothesis is verified in the current trial, sublobar resection will be demonstrated to achieve equivalent therapeutic outcomes compared with lobectomy for elderly patients (≥70 years) with NSCLC at an early stage, with respect to DFS time, hospital stay, intubation time, peri-operative complication, death rate, overall survival rate, recurrence and metastasis rates within post-operative 3 and 5 years, and pulmonary function 6, 12, and 36 months after operation, respectively.

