## Abstract

**Background:**

The appropriateness of lobectomy for all elderly patients is controversial. Meanwhile, sublobar resection is associated with reduced operative risk, better preservation of pulmonary function, and a better quality of life, constituting a potential alternative to standard lobectomy for elderly patients with early-stage non-small cell lung cancer (NSCLC). To date, no randomized trial comparing sublobar resection and lobectomy focusing on elderly patients has been reported. We hypothesized that for patients at least 70 years old with clinical stage T1N0M0 NSCLC, sublobar resection is non-inferior to lobectomy for 3-year disease-free survival (DFS).

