**Methods/design:**

This is a prospective, randomized, controlled multicenter non-inferiority trial with two study arms: sublobar resection and lobectomy groups. Comprehensive geriatric assessments will be acquired for each patient. A total of 339 subjects will be enrolled on the basis of power calculations, and participants followed up every 6 months post-operation for 3 years. In case of relapse, survival follow-up will be continued until 5 years or death. Pulmonary function testing will be performed at 6, 12, and 36 months post-operation. The primary outcome is 3-year DFS; secondary endpoints include peri-operative complications and mortality, hospitalization time, post-operative ventilator time, overall survival, 3-year recurrence rates, post-operative pulmonary function, quality of life, geriatric assessment data, and 4-year mortality index.

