Lobectomy is not the only option for elderly patients with early-stage NSCLC. Several retrospective studies supported sublobar resection, including segmentectomy and wedge resection, as a sound alternative for the elderly. A retrospective study from the SEER database analyzing 14,555 patients with NSCLC stage I/II suggested that lobectomy conveys benefits only patients younger than 71 years [24]. Similarly, at Pittsburgh Medical Center, Kilic et al. indicated that segmentectomy is associated with reduced peri-operative complications (29.5 % versus 50 %) in patients over 70 years with stage I NSCLC but that local recurrence and overall survival rates are not significantly different [25]. A retrospective study from Japan found that 5-year survival after sublobar resection is significantly inferior to that after standard lobectomy (64.0 % and 90.9 %, respectively, *P* < 0.0001) in the younger group (median age of 68 versus 64); however, in the elderly (median age of 78 versus 77), no substantial difference was observed (67.6 % and 74.3 %, *P* = 0.92) [26]. These data demonstrated that sublobar resection might achieve equivalent benefits compared with lobectomy for the elderly and that the gap in long-term outcome between sublobar resection and lobectomy might shrink as patient age increases. Additionally, sublobar resection may play a better role in preserving the lung function [27, 28], which is important for patients with small lung cancer, conferring long survival, considering the possibility of further lung resections to treat second primary lung tumors.

In summary, sublobar resection may be an alternative to standard lobectomy for elderly patients with early-stage NSCLC, resulting in less operative risk, better preservation of pulmonary function, and improved quality of life (QoL), without compromising survival. However, trials dedicated to surgical assessments are scarce in elderly patients, who comprise a large percentage of all patients.

This randomized trial is, to the best of our knowledge, the first designed to compare sublobar resection and lobectomy for elderly patients in order to address the following open questions: whether in patients at least 70 years old with clinical stage T1N0M0 NSCLC (1) sublobar resection can achieve similar disease-free survival (DFS) compared with lobectomy, (2) sublobar resection can reduce post-operative mortality and morbidity, and (3) sublobar resection can yield better pulmonary function and QoL.

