## Methods

### Trial design

The Surgical Treatment of Elderly Patients with early-stage non-small cell lung cancer (STEPS) study was designed as a prospective, randomized, controlled, multicenter non-inferiority trial with two parallel study arms. The hypothesis was that for patients 70 or over with clinical stage T1M0M0 NSCLC, sublobar resection could achieve non-inferior 3-year DFS.

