### Sample size

Sample size was calculated by the PASS (Power Analysis and Sample Size) software, based on 3-year DFS of elderly patients. There were no exact published data about the DFS rate at 3 years of elderly patients with stage I NSCLC [33, 34], and we estimated the DFS rate at 3 years for lobectomy (control group) to be approximately 75 %. DFS rate at 3 years of 60 % for sublobar resection is considered unacceptable. Under our current assumption, the 15 % of non-inferiority margin on DFS at 3 years corresponds to a hazard ratio of 1.78. The sample-size calculation was based on log rank test. The calculated sample size was 339 patients, and event number of 96 was based on an estimated post-operative 3-year DFS rate of 75 %, 10 % non-compliance, 3-year open enrolment period, 3-year follow-up period, and one-sided type I error rate of 0.025 with 90 % statistical power.

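### The Discussion turns one DFS non-inferiority result into demonstrated equivalence on DFS and several named secondary outcomes, which the planned test cannot show

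*Protocol article*

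**What the plan says.** All places are in the protocol article.

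- **Hypothesis.** Trial design states only that "sublobar resection could achieve non-inferior 3-year DFS"; the Abstract agrees.
- **Margin and size.** Sample size is "based on 3-year DFS of elderly patients". It takes 75 % for lobectomy, treats 60 % for sublobar resection as unacceptable, and gives a 15-point margin equal to a hazard ratio of 1.78, one-sided type I error 0.025, 339 patients and 96 events. No other margin appears in the article.
- **Conclusion announced.** Near its end, the Discussion says that if the hypothesis is verified, "sublobar resection will be demonstrated to achieve equivalent therapeutic outcomes compared with lobectomy for elderly patients". The scope is "with respect to DFS time, hospital stay, intubation time, peri-operative complication, death rate, overall survival rate, recurrence and metastasis rates within post-operative 3 and 5" (counted in years); the list then adds pulmonary function at 6, 12 and 36 months.
- **Aims.** The last paragraph of the Background asks, besides DFS, whether "sublobar resection can reduce post-operative mortality and morbidity" and whether "sublobar resection can yield better pulmonary function and QoL".
- **Follow-up.** Secondary endpoints define recurrence and metastasis at 3 years. Chest CT runs every 6 months for 3 years (Post-operative follow-up). Telephone contact to 5 years applies only after recurrence (Survival follow-up).

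**The concern.** The Discussion sentence says in advance what a positive trial will mean, and that meaning goes well beyond the test. One non-inferiority result on one endpoint would be read as proof that the operations are equivalent on a list of separate outcomes, some clinical, some functional, one with a 5-year horizon.

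Two wrong conclusions could follow. Overall survival or recurrence could be called equivalent when the comparison is merely imprecise. Complications or lung function could be called equivalent when they differ, including when they differ in the direction the trial hopes for. The second error matters for the rationale: the Background and Discussion present sublobar resection as a trade of some radicality for lower operative risk and better function. A conclusion of equivalence on risk and function leaves out the benefit side of that trade.

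**Working it through.** **1. The margin.** Under proportional hazards, 75 % v 60 % at 3 years gives ln(0.60)/ln(0.75) = 0.5108/0.2877 = 1.776. The stated 1.78 reproduces. (The 96 events do not match 90 % power by the Schoenfeld formula, which needs 127 to 128; 96 gives about 80 %. That is a separate matter and does not affect this point.)

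**2. What a positive DFS test shows.** With 96 events and 1:1 allocation (assumed; the article does not state the ratio), the standard error of the log hazard ratio is 2/√96 = 0.204. The upper 95 % limit is the observed ratio times exp(1.96 × 0.204) = 1.492. Non-inferiority is therefore met by any observed ratio up to 1.78/1.492 = 1.19, with no lower bound. Equivalence would need a lower limit too.

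For illustration, take a symmetric range of 1/1.78 to 1.78, each side at one-sided 0.025, and a true ratio of 1:

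- Non-inferiority power: Φ(ln 1.78 × √96/2 − 1.96) = Φ(0.865) = 0.81.
- Equivalence power: 2 × 0.81 − 1 = 0.61 (0.613 unrounded).

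So the planned test is not an equivalence test even for DFS.

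**3. Complications.** The Background cites 29.5 % v 50 % from a retrospective comparison of segmentectomy in patients over 70. With 339/2 ≈ 169 per arm:

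- Difference: 50 − 29.5 = 20.5 points.
- 95 % half-width: 1.96 × √(0.50 × 0.50/169 + 0.295 × 0.705/169) = 0.102, so the interval is about 10.3 to 30.7 points.
- Power to show a difference at two-sided 0.05: about 97 % (about 96 % with 152 per arm, after 10 % non-compliance).

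This result could occur together with DFS non-inferiority. The sentence would then call equivalent what the data show to be different.

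**4. Overall survival.** The article gives no expected 3-year rate, so 85 % in both arms is an assumption. The 95 % half-width for the difference is 1.96 × √(2 × 0.85 × 0.15/169.5) = 0.076, or 7.6 points. It is 6.4 points at 90 % and 8.5 at 80 %. Without a margin, an interval of that width around no difference does not establish equivalence.

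**5. Five-year recurrence.** The endpoint is defined at 3 years, scheduled imaging ends at 3 years, and later contact covers only patients who have already relapsed. A first recurrence in years 3 to 5 in a patient disease-free at 3 years would not be found systematically.

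**6. Direction of inference.**

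| Outcome | Background asks | Discussion would conclude |
|---|---|---|
| Mortality and morbidity | Reduced? | Equivalent |
| Pulmonary function | Better? | Equivalent |
| Quality of life | Better? | Not named |

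**The case against.** The strongest reply is that this is one loosely worded closing sentence in a journal article and not an analysis rule. The operative text is consistent: hypothesis, primary endpoint, margin and sample size all concern DFS, and Statistical methods plan hazard ratios with 95 % confidence intervals. That stands. No test, endpoint or data collection depends on the sentence; what it would distort is the conclusion drawn from a positive result.

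Several stronger readings are tempting and are not supported:

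- **That equivalence is claimed on all secondary outcomes.** The sentence does not name quality of life, the proportion of video-assisted procedures, or the geriatric assessment and 4-year mortality index. The conflict with the Background therefore does not extend to quality of life.
- **That two fixed rules contradict each other.** The Background poses open questions. The conflict is one of direction of inference.
- **That a DFS loss just short of 15 points would readily pass.** At 96 events the observed ratio must be about 1.19 or less. Against 75 %, that is 0.75^1.19 ≈ 71 %, an observed deficit of about 4 points. A true loss at the margin would pass only about 2.5 % of the time.
- **That a fixed testing order for secondary outcomes is missing.** Such ordering is commonly left to the analysis plan. Gating complications behind DFS would also clash with Statistical methods, which analyse peri-operative data when recruitment is complete and survival data only at trial end.

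**Conclusion.** The point holds in this form: verifying one-sided non-inferiority of 3-year DFS does not demonstrate equivalence on DFS, nor on the other outcomes the Discussion names. For those other outcomes the article gives no margin or equivalence test, and for 5-year recurrence and metastasis the planned follow-up does not supply the data.

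The error can be large. With the cited complication rates, the trial would very probably (about 97 %) show a difference that the sentence calls equivalence. That figure rests on 1:1 allocation and on retrospective segmentectomy rates applying here, where wedge resection is also allowed. The overall-survival width rests on an assumed rate of 80 to 90 %. The main conclusion needs none of these assumptions: it follows from the stated hypothesis and the single stated margin. The primary analysis is unaffected, but the sentence should be corrected because following it would give a wrong conclusion.

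**What to change.** - In the Discussion, limit the conclusion from a verified hypothesis to non-inferiority of 3-year DFS within the 15-point margin (hazard ratio 1.78).
- Delete the equivalence claim for the other named outcomes, and the claim about 5-year recurrence and metastasis.
- Report complications and pulmonary function as tests of difference, in line with the Background's questions.
- Report the other secondary outcomes as estimates with 95 % confidence intervals, and state that a non-significant difference will not be read as equivalence.

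This needs no additional patients, visits or data. The cost is a narrower claim.

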### Current status

The trial has received ethics approval, and enrollment in the trial has begun but has not yet reached full enrollment.

## Abbreviations

ASA: American Society of Anesthesiologists
CGA: Comprehensive geriatric assessment
CRF: Case report form
CT: Computed tomography
DFS: Disease-free survival
LCSG: Lung Cancer Study Group
NSCLC: Non-small cell lung cancer
PACE: Pre-operative assessment of cancer in the elderly
QoL: Quality of life
SEER: Surveillance, Epidemiology, and End Results
VES-13: Vulnerable Elders Survey
